# Efficacy of a Digital Acceptance and Commitment Therapy Intervention for the Improvement of Self-management Behaviors and Psychological Flexibility in Adults With Cardiac Disease: Protocol for a Single Case Experimental Design

**DOI:** 10.2196/33783

**Published:** 2022-04-01

**Keywords:** cardiac disease, acceptance and commitment therapy, distress management, self-management, single case experimental design, digital health

## Abstract

**Background:**

Research indicates that the management of distress levels in those with cardiac disease is not only important for improving quality of life and functioning but also critical for condition management; adherence to treatment; and, ultimately, disease prognosis and progression. Acceptance and commitment therapy (ACT) has consistently demonstrated positive long-term outcomes across a wide array of conditions, including chronic illness. However, most empirical investigations conducted to date have also involved in-person therapy, which can be difficult to access, particularly for those dealing with the demands of chronic disease.

**Objective:**

The objective of our research is to evaluate a digital ACT intervention for improving self-management behaviors and distress levels in those with cardiac conditions.

**Methods:**

The digital ACT intervention will be delivered via a digital health self-management platform over 6 sessions. This will involve a randomized, multiple baseline, single case experimental design with approximately 3 to 15 adults with cardiac disease. The independent variable for each participant will be the pre-post intervention phase. The dependent variables will be a daily self-report measure of psychological flexibility as well as objective measures of condition self-management (eg, blood pressure readings) and engagement with the app (eg, completing guided mindfulness). One-to-one qualitative interviews will also be conducted to further examine participants’ experiences with using the intervention and what factors contribute to or impede successful outcomes.

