### Design

Our research will involve a mixed methods design, which will include a nonconcurrent, randomized, multiple baseline SCED and one-to-one qualitative interviews. SCEDs treat each participant as a separate experiment in which data are collected at multiple time points for each participant and subsequently meta-analyzed across participants. This type of design is well suited to research involving niche or difficult-to-reach populations and provides advantages over group designs by examining the variability within and the experimental control of an individual’s behavior as opposed to using group means [37,38]. The independent variable for each participant will be the pre-post intervention phase, and the dependent variables will be self-report measures of psychological flexibility, objective measures of self-management, and engagement with symptom and lifestyle parameter monitoring. The intervention will be randomly staggered across participants. Prior to the intervention being administered, baseline data will be collected from each participant for 2 weeks or until a stable baseline score is established for dependent variables, at which point the intervention will be introduced. At 1 week after the introduction of the intervention (or sooner), should an effect be observed, the next participant will begin to complete the baseline data collection process, and this will continue until the intervention is introduced to all participants. Randomization periods of 5 to 7 days are recommended [39].

Consistent with the aim of CBS, that is, to examine outcomes of interest at multiple levels of evidence analysis by using various methods [40], quantitative findings will be triangulated by using qualitative interviews wherein more detailed insights into each participant’s experience with the trial will be examined.

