### Procedure

Upon agreeing to participate in the study and once informed consent is obtained, participants will receive an Apple iPad (8th Gen, 10.2-inch, Wi-Fi, 32GB; Apple Inc) with the ECME-ACT app installed as well as digital devices for monitoring symptoms and lifestyle parameters of relevance to their cardiovascular condition. Participants will either meet the researcher in their homes or in the research center (depending on their preferences and availability) wherein they will receive the devices and be verbally instructed on how to use them in addition to being provided with the relevant user manuals. Upon receiving the app (but prior to the ACT intervention being administered), baseline data for digital self-management behaviors and the self-report measure of psychological flexibility (see *Measures* section) will be collected for each participant over a 2 week period or until a stable baseline score is established. A multiple baseline SCED will be used, wherein the intervention will be staggered across participants (Figure 1).

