### Measures

The Brief Acceptance Measure [42] is a 3-item self-report measure of psychological flexibility that was designed specifically for use in SCEDs. Participants will complete this daily within the app and will be sent a reminder to do so via a text message (sent by the primary researcher).

Symptom and lifestyle data and engagement with monitoring will be logged via the digital app for relevant self-management behaviors (eg, monitoring blood pressure and inputting weight). Participants will also receive a daily text message reminder to take readings. Engagement with the digital app will also be logged to ascertain the number of times that the participants use the app and its various features.

One-to-one interviews will examine participants’ experiences with the intervention and explore the following:

How are quality of life and day-to-day functioning following the completion of the intervention?What factors facilitated or impeded the ability to engage with the intervention?What changes to the intervention, if any, would participants make?If applicable, what factors lead the participant to discontinue their use of the digital intervention?

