### ACT Intervention

The intervention used in the study will be based on the *Acceptance and Commitment Therapy (ACT) Training Manual for Stress Reduction in Patients with Inflammatory Bowel Disease (IBD)* protocol [43], which will be adapted for use with cardiac conditions as opposed to inflammatory bowel disease. This protocol outlines a 6-session ACT intervention for populations with chronic illness with once-weekly sessions (approximately 1 hour). The intervention in this study will be delivered via Zoom by a peer-reviewed ACT trainer and expert and the lead researcher. Participants will also be provided with psychoeducation and mindfulness exercises (homework) via the digital app to help them implement and practice the strategies that they have learned throughout their day-to-day lives.

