#### ECME-ACT App

The ECME-ACT app is the responsive web-based app on which participants will engage with data from digital health devices, including blood pressure, heart rate, weight, activity, and sleep (Figure 2), and features related to the digital ACT intervention (specifically, guided mindfulness audio recordings, psychoeducation and tips [Figure 3], and daily self-report measures [Figure 4]). The design of the digital app is based on findings from previous research, including interviews and co-design sessions, involving older adults with cardiac conditions [36,44]. Participants will be provisioned with an iPad for the duration of their participation in the study, through which they will engage with the ECME-ACT app and participate in the one-to-one therapeutic sessions conducted via Zoom.

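### App engagement, exemplified by completing guided mindfulness, is listed as an A-B outcome although guided mindfulness is part of the intervention; a phase contrast on it measures receipt of treatment

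*Protocol article*

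**What the plan says.** The protocol article describes the engagement outcome in three places, and the three do not match.

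- **Abstract, Methods.** The contrast is between phases: "The independent variable for each participant will be the pre-post intervention phase". The dependent variables include "engagement with the app (eg, completing guided mindfulness".
- **Design.** The dependent variables are psychological flexibility, "objective measures of self-management, and engagement with symptom and lifestyle parameter monitoring". ACT features are not mentioned.
- **Measures.** "Engagement with the digital app will also be logged to ascertain the number of times that the participants use the app and its various features". ACT features are not separated from monitoring features.

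Two other sections place guided mindfulness inside the treatment. ACT Intervention states: "Participants will also be provided with psychoeducation and mindfulness exercises (homework) via the digital app". ECME-ACT App lists "features related to the digital ACT intervention (specifically, guided mindfulness audio recordings, psychoeducation and tips".

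On timing, Procedure says: "Upon receiving the app (but prior to the ACT intervention being administered), baseline data for digital self-management behaviors" and the psychological flexibility measure are collected. Participants therefore hold the app throughout baseline. The article does not say whether the mindfulness and psychoeducation features can be opened in that period.

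**The concern.** An outcome in an A-B design has to be something that could take any of its values in either phase, so that a change can be credited to the intervention. Playing a mindfulness recording that the therapist has set as homework is exposure to the intervention. Compared across phases, it answers whether participants did the homework once it was set. It does not answer whether self-management or psychological flexibility improved.

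The Quantitative Analysis section plans exact tests and meta-analysed effect sizes for A-B data. If engagement as worded in the abstract goes through that analysis, the report could show a large, consistent effect that carries no information on efficacy, next to outcomes that do carry it.

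**Working it through.** The article gives no effect size, alpha or power for this outcome, so there is no figure to reproduce. The check has three steps.

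**1. Can the variable be measured in both phases?**

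| Variable | Where named | Phase A | Phase B |
|---|---|---|---|
| Engagement with monitoring | Design | available | available |
| ACT-feature use (eg, mindfulness) | Abstract | absent, or use is exposure to ACT content | homework |
| Total app use | Measures | monitoring, daily questions | the same plus homework |

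Only the first row gives a clean contrast.

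**2. What the contrast estimates.** Let qA and qB be the daily probability of using an ACT feature in each phase.

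- Features start with phase B: qA = 0, so the expected difference is qB − 0 = qB. It is uptake, and it cannot be below zero.
- Features open in baseline: the difference is qB − qA, and any qA above zero is ACT content received in phase A.
- Total app use: let m be daily opens for monitoring and questions, and h the extra opens for homework. The expected difference is (mB − mA) + h. With no change in monitoring (mB = mA) it equals h, which is positive whenever homework brings opens of its own.

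**3. How large this could look.** Inputs from the article: 14 baseline days (Design: 2 weeks, or until stable), a 7-day start window (Design: 5 to 7 days), and N of 3, 10 or 15 (Recruitment). Six weekly sessions were taken as at least 42 phase B days. All q values are assumptions.

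Daily yes/no use was simulated. Each participant had a start-point randomization test on the mean difference. The p-values were combined by Edgington's additive method, one-sided at 0.05, with 1,000 runs per cell. Non-overlap of all pairs (NAP) for a yes/no variable is 0.5 + 0.5 × (qB − qA); for example, 0.5 + 0.5 × 0.5 = 0.75.

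| qA | qB | Mean difference | NAP | Participants with difference > 0 | Rejects, N=3 | N=10 | N=15 |
|---|---|---|---|---|---|---|---|
| 0 | 0.1 | 0.10 | 0.55 | 99.1% | 4.4% | 7.5% | 8.8% |
| 0 | 0.3 | 0.30 | 0.65 | 100% | 17.9% | 65.2% | 78.6% |
| 0 | 0.5 | 0.50 | 0.75 | 100% | 42.9% | 97.2% | 99.9% |
| 0 | 0.7 | 0.70 | 0.85 | 100% | 69.9% | 100% | 100% |
| 0.3 | 0.5 | 0.20 | 0.60 | 92.6% | 7.0% | 8.9% | 11.9% |
| 0.5 | 0.5 | 0.00 | 0.50 | 49.4% | 0.8% | 0.4% | 0.1% |

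The last row shows that, with only seven start points, the combined test is conservative: it rejects well under 5% of the time when nothing changes. With qA = 0, the direction is settled by design in almost every participant, while significance follows uptake. The same phase B behaviour (qB = 0.5, N = 10) gives 97.2% rejection if baseline use was impossible, 8.9% if it was 0.3, and 0.4% if it was 0.5. The result turns on feature access and homework compliance; self-management does not enter the simulation at all.

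**The case against.** The strongest reply is that the Methods already have it right. Design words the outcome as engagement with monitoring. Procedure limits baseline collection to self-management behaviors and psychological flexibility. The predictions at the end of the Introduction and in the Discussion concern self-management, adherence and psychological flexibility, not mindfulness use. On this view the problem is one example in the abstract, and the logging described under Measures need not imply a phase test.

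Much of this stands. It narrows the point to one secondary outcome and supplies the right definition. It does not remove the point: the abstract explicitly calls the variable dependent and sets it against phase, and Measures does not settle which counts will be compared. A fuller protocol might state when the features became available, but that would not turn ACT-feature use into a valid A-B outcome.

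A reader might go further and infer that baseline is contaminated with ACT content, so that the psychological flexibility comparison is biased toward no effect. The article does not support that. Procedure places baseline before the ACT intervention, and ACT Intervention presents the app exercises as homework for strategies learned in the sessions. The natural reading is that this content begins with phase B. Access in baseline is simply not stated, and a condensed article may leave that to the full protocol.

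**Conclusion.** The concern holds in a limited form. The abstract and the Design section disagree on the engagement outcome, and the abstract's version counts part of the treatment as a response to it. If the features begin with phase B, the difference equals uptake and is never negative. With 10 to 15 participants and homework on half of the days, it would be declared significant in 97% to 99.9% of simulated trials. At one day in ten the figure is 7.5% to 8.8%.

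These percentages rest on assumed use rates and an assumed 7-day window, with at least 42 phase B days; they illustrate the mechanism and do not forecast this trial. A reader might infer that any use at all guarantees a significant result, or that phases would not overlap at all. Neither follows: only the direction is fixed, and complete non-overlap needs use on every phase B day. Psychological flexibility and the monitoring outcomes are unaffected if the features begin with phase B.

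**What to change.** 1. Reconcile the Abstract, Design and Measures. Define the A-B engagement outcome as use of monitoring functions available in both phases, for example days with a blood pressure reading.
2. Remove ACT-feature use (mindfulness audio, psychoeducation, tips) and total app opens from the A-B dependent variables. Report them as phase B uptake, without a phase test.
3. State whether ACT features were accessible during baseline. If they were, report each participant's baseline use as exposure and read the psychological flexibility result with it in view.

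Data collection began in October 2021, so locking features now could not alter baselines already completed. The redefinition can still be applied to every participant, provided the logs keep dated counts by feature; Measures says that use of the various features is logged. No new data are needed. The price is the loss of one secondary outcome that would probably have looked favourable.

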**Results:**

Participant recruitment and data collection began in October 2021, and it is projected that the study findings will be available for dissemination by spring 2022.

**Conclusions:**

The findings will be discussed in terms of how a digital ACT intervention can best meet the needs of cardiac patients.

**International Registered Report Identifier (IRRID):**

PRR1-10.2196/33783

## Introduction

Chronic illnesses typically result in a complex set of symptoms and demanding lifestyle adjustments, with upwards of 30% of individuals with 1 or more chronic health conditions also experiencing a clinically significant mental health concern [1]. Cardiac disease in particular is linked to high levels of depression and anxiety [2-4]. Even more concerning is that depression and anxiety are associated with poor treatment adherence, poor functionality, increased hospitalization rates, and increased mortality risk across studies [5-7].

To date, cognitive behavioral therapy (CBT) is the most widely tested psychotherapeutic approach for patients with chronic conditions in the psychology literature. Although CBT has been associated with improved mood and quality of life as well as decreased symptoms of depression and anxiety [8-10], positive psychological and mood outcomes have not been consistently observed in people with chronic health conditions [11]. Many therapeutic approaches, including CBT, strive to achieve emotional and behavioral change by attempting to change or suppress “faulty” thoughts. For those with chronic conditions, this is unlikely to be feasible, particularly because condition management requires participants to engage with and report on their symptoms in an honest manner, and attempts to suppress and avoid difficult thoughts and feelings regarding symptoms can be invalidating and disempowering and may lead to or increase the avoidance of self-management behaviors [12].

In order to meet the complex needs of those with cardiac disease and to develop more effective psychotherapeutic interventions for the improvement of mental well-being, adherence, and self-management behaviors in these populations, a transdiagnostic approach (ie, universally applicable treatment regardless of a condition or diagnosis) that reduces avoidance and results in lasting outcomes is needed. One such approach may be found under the remit of contextual behavioral science (CBS).

CBS is a psychological science that provides in-depth and theoretically coherent explanations of complex human behaviors [13,14]. The clinical application of CBS is known as *acceptance and commitment therapy* (ACT) [15], and its therapeutic aim is to foster a process known as *psychological flexibility*. Hayes et al [16] reported the following definition of psychological flexibility: “the ability to contact the present moment more fully as a conscious human being, and to change or persist in behavior when doing so serves valued ends.” Distress reduction is not a goal in ACT; rather, it enables an individual to engage in a fully meaningful life despite the presence of distress by reducing ineffective behaviors and issues related to using thoughts and feelings as reasons for exhibiting or avoiding certain behaviors. ACT involves using a transdiagnostic approach, and over the last 30 years, empirical support has been observed for its use in managing a plethora of conditions, including but not limited to depression, anxiety disorder, stress, chronic illness, diabetes, addiction, chronic pain, and distress reduction in patients with cancer [16-18]. Further, even when presented in a very brief form, ACT results in positive outcomes for chronic conditions [19,20].

Despite the large body of literature demonstrating the efficacy of ACT for mental health concerns, chronic pain, and other conditions [17,18,21], there have only been a small number of investigations into ACT interventions for chronic disease conditions. However, desirable results from ACT have been observed for reported well-being, quality of life, adherence, and self-management behaviors across a range of populations, including those with diabetes, HIV, colorectal cancer, inflammatory bowel disease, obesity, and other health conditions [22-28]. To the best of our knowledge, there has only been 1 study published to date that explores the feasibility of ACT with a population of cardiac patients. Goodwin et al [29] conducted a feasibility study wherein 16 cardiac patients (12 following the drop out of 4 participants), who were mostly of lower socioeconomic status, completed 4 ACT workshops. Each workshop was conducted for 90 minutes. Large to medium improvements were observed for measures of patients’ adherence to healthy lifestyle behaviors, including weight loss, increased physical activity, and improved diet. Similarly, significant or near significant improvements were observed for psychological self-report measures of acceptance, awareness, and cognitive defusion (ie, the undermining of unhelpful thought patterns). However, due to low power and the lack of a control condition, these findings must be considered tentatively, but these preliminary results are promising [29].

A systematic review by Graham et al [30] identified a number of investigations into ACT interventions for chronic health conditions that demonstrated promising findings, including improved psychological flexibility, medication adherence, and disease self-management. Poor study quality was a considerable issue, with many studies being underpowered and lacking a control condition and the authors calling for more rigorous investigations. Most empirical investigations conducted to date however have involved in-person therapy, which typically can be expensive, time-consuming, and difficult to access, especially for those dealing with the demands of chronic disease [31]. Interventions delivered in the form of a digital application may offer a solution for these problems. Although such interventions have not been extensively investigated among patients with chronic diseases, there are promising findings emerging [27,32,33].

In addition to being more cost- and time-effective [34], web-based and digital interventions have also been shown to increase health literacy and knowledge and improve coping [35]. ACT seems particularly effective when used in combination with health education and training [23], therefore making it particularly well suited for use in the management of chronic conditions.

The aim of our study is to investigate the efficacy of a digital ACT intervention for the improvement of self-management behaviors, adherence, and psychological flexibility in a sample of participants with cardiac disease. The study will use a digital self-management platform that was developed and rigorously tested in large-scale trial with older adults with chronic health conditions, ensuring its suitability for use with such populations [36]. This technology supports participants in monitoring and reviewing symptom (eg, blood pressure, heart rate, and weight) and lifestyle parameters (eg, activity) that are relevant to their conditions and has been updated to include a newly designed app (ECME [Eastern Corridor for Medical Engineering Centre]-ACT; described further in the *Digital Platform* section). The platform also captures data on participants’ engagement with devices as well as readings, therefore providing objective measures of target behaviors in real time. Participants will also complete a daily self-report measure of psychological flexibility.

Given the transdiagnostically applicable nature of ACT, our research will examine its suitability for all levels of disease severity and progression, with the goal of developing an intervention that will (1) increase engagement with relevant preventive behaviors among people with less severe cardiac disease (eg, hypertension) and (2) provide sufficiently high treatment dosages to those with more profound levels of disease (eg, advanced heart failure), who may require a lot of distress management. Therefore, individuals who have been diagnosed with any type or stage of cardiac disease will be invited to participate in the research.

Due to both the specific nature of the population under investigation and the fact that measures must be completed on a daily basis, our study will use a randomized, multiple baseline, single case experimental design (SCED). SCEDs offer practical and effective solutions by providing high-quality evidence for the efficacy of an intervention and using a considerably smaller sample than that of a randomized controlled trial. Such a design is particularly well suited to examining health and lifestyle behaviors in real time in the context of participants’ daily lives to provide more accurate insights into how and when behavior change occurs. This can help to identify which intervention components are active (and which are not active) in producing meaningful changes.

Given the complexity of symptoms and varying levels of disease severity and prognoses among individuals with cardiac conditions, as well as the wide range of contextual factors that impact outcomes, it is important to understand these individuals’ varying needs and how they may best be met. On this basis, participants will be invited to participate in one-to-one interviews upon their completion of the program to explore in further detail the factors that contributed to or impeded successful engagement with the overall intervention and any potential issues that arose. It is predicted that self-management behaviors will improve and that psychological flexibility will increase following the completion of the digital ACT intervention.

